### Inclusion and Exclusion Criteria

Cases will be defined as children who are stunted, reside in the study area, are aged 6 months to 5 years, with a mother or father as the caregiver, reside in a household with or without livestock, and are willing to participate and follow the requirements of the study. Controls will be defined as children who are not stunted, residents of the same study area, aged 6 months to 5 years, with a mother or father as the caregiver, who reside in a household with or without livestock, and are ready to participate and follow the requirements of the study. Children will be excluded from the study if they exhibit any obvious congenital defect, have a major medical condition, or need a prolonged hospital stay after birth. Those who have not lived in the Wardha district for at least the past 3 months and those presently involved in another study on animal husbandry will also be excluded.

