### Sample Size

The study will involve participants chosen based on specific inclusion and exclusion criteria. It will include all children younger than 5 years from the respective villages. Considering the overall number of children younger than 5 years in the Wardha rural area sample, the total population was 88,224 children [20].

Estimated sample size = n≥(NZ_(1-α⁄2)^2 p(1-p))/(d^2 (N-1)+Z_(1-α⁄2)^2 p(1-p)), where α (a)=.05; estimated proportion of children younger than 5 years who are stunted (height-for-age) *P*=.28 [9]; and estimation error (d) = 5% = 0.05. The minimal sample size calculated for this study will be 614, of which 307 are cases and 307 are controls, considering the ratio of case-control is 1:1.

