To calculate the total number of livestock, a standardized unit must be used to represent the livestock counts for all species. A TLU is a standard unit that allows for the comparison of various species of varying sizes by using a common measure. Conversion equivalents of livestock into TLU are mentioned in Table 1 for households with livestock ownership [21].

**Table 1 table1:** Conversion equivalents of livestock into Tropical Livestock Unit [16].

Species (animal type)	Tropical Livestock Unit equivalent
Cattle (bull)	1.0
Cattle (cow/buffalo)	0.8
Cattle (calves)	0.2
Sheep/goats	0.1
Horses	0.8
Donkeys/mules	0.5
Poultry	0.01

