### Data Analysis

All the results will be calculated using RStudio software (version 4.3.2; Posit). The complete analysis dataset will consist of all study participants who have no missing data for any of the variables in the dataset. The study participants will be those individuals who meet the criteria for inclusion and exclusion. Baseline characteristics will be utilized to compile all the data, representing demographic variables with mean and standard deviation for continuous data and frequency and percentage for categorical data. The results will be examined for continuous data, which will be described using the minimum, maximum, average, standard deviation, standard error, and 95% CI for parametric data. The normality of the continuous outcome variables will be assessed initially with the Kolmogorov-Smirnov test at a 5% significance level (*P*≤.05). If the data are not rejected, a nonparametric test will be used to determine significance; otherwise, it will be considered normal. The significant difference at the 5% level (*P*≤.05) between stunted and nonstunted comparative groups will be determined using a 2-sided *t* test. Nonnormal data will be summarized using mean, median, and lower and upper quartiles for nonparametric testing and will be assessed for significance using the Mann-Whitney test. Categorical variables will be presented with frequency (n) and percentage value (%). The categorical variables (stunted and nonstunted) will be analyzed by Fisher exact test to find significant associations of different risk factors. All confounding variables will be analyzed using multivariable logistic regression. Associated risks will be investigated and tabulated using the odds ratio with a confidence interval. To understand the effects of multiple factors, confounding variables will be recognized and adjusted to understand the multiple factors that can influence the outcome (stunting). For the confounding effect, multivariable methods will be employed to estimate the association between exposure (livestock) and outcome (stunting), or the impact of one or more confounding factors such as WASH; wealth index of the household; episodes of illness; dietary habits; knowledge, attitude, and practices regarding livestock; and livestock diseases will be considered. Essentially, multivariable logistic regression will allow assessing the independent effect of each of the exposures.

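### The normality decision rule is written backwards and contradicts the Mann-Whitney sentence in the same paragraph

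*Protocol article*

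**What the plan says.** All the relevant text is in one paragraph of the protocol article, under Data Analysis.

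- The pretest: "The normality of the continuous outcome variables will be assessed initially with the Kolmogorov-Smirnov test at a 5% significance level".
- The decision rule: "If the data are not rejected, a nonparametric test will be used to determine significance; otherwise, it will be considered normal".
- The parametric comparison: the difference "between stunted and nonstunted comparative groups will be determined using a 2-sided" t test.
- The nonparametric comparison: "Nonnormal data will be summarized using mean, median, and lower and upper quartiles for nonparametric testing and will be assessed for significance using the Mann-Whitney".

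The same paragraph assigns the Fisher exact test to categorical variables and multivariable logistic regression to the adjusted association between livestock and stunting. Neither depends on the normality rule. No other section restates or corrects the rule.

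**The concern.** A normality test that does not reject gives no evidence against normality. The plan responds to that result with a nonparametric test, and responds to a rejection by treating the variable as normal. Both branches are the wrong way round.

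The paragraph then gives nonnormal data to the Mann-Whitney test. An analyst therefore has two instructions that cannot both be followed for a variable that fails the normality test. One must be dropped, and unless the text is corrected that choice could be made after the data are seen. At stake are the test and the accompanying summary statistics for every unadjusted continuous comparison between stunted and nonstunted children.

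**Working it through.** **1. The logic, with no assumptions.** The Kolmogorov-Smirnov null hypothesis is that the variable is normally distributed.

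| Kolmogorov-Smirnov result | Meaning | Decision rule as written | Later sentences of the paragraph |
|---|---|---|---|
| Not rejected | No evidence against normality | Nonparametric test | t test (implied) |
| Rejected (P ≤ .05) | Evidence of nonnormality | Treated as normal, hence t test | Mann-Whitney |

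The two right-hand columns disagree in both rows. The test has no form in which rejection supports normality, so no reading of the word rejected rescues the rule.

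**2. The plan's own sample size**, used here only to set n for the illustration. Inputs from Sample Size: N = 88,224, p = 0.28, d = 0.05; Z = 1.96.

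n = N Z² p(1−p) / [d²(N−1) + Z² p(1−p)]

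- Z² p(1−p) = 3.8416 × 0.2016 = 0.77447
- Numerator: 88,224 × 0.77447 = 68,326.5
- Denominator: 0.0025 × 88,223 + 0.77447 = 221.332
- n = 308.7, or 309 per group and 618 in total

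The stated figures are 307 and 614, which is close enough for this purpose. Nothing below turns on the difference.

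**3. Where the rule sends data at n = 614.** The article gives no distribution for any continuous variable, so the shapes are assumptions. The TLU-like shape has half the households as non-owners (TLU = 0). Owners have 0.8 × Poisson(1) + 0.1 × Poisson(1) + 0.01 × Poisson(3), using three of the weights in Table 1. There were 1,000 runs for the Kolmogorov-Smirnov test with estimated mean and SD, and 300 for its Lilliefors correction.

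| Assumed shape | Normality rejected | Test under the rule as written | Test if reversed |
|---|---|---|---|
| Normal | 0% (2.7% with Lilliefors) | Nonparametric in about 97–100% | t test in about 97–100% |
| Lognormal, log-SD 1 | 100% | t test in 100% | Mann-Whitney in 100% |
| TLU-like | 100% | t test in 100% | Mann-Whitney in 100% |

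**4. What the swap does at 307 per group, two-sided 5%** (2,000 runs each).

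| Assumed shape | Type I error, t test | Type I error, Mann-Whitney | Alternative | Power, t test | Power, Mann-Whitney |
|---|---|---|---|---|---|
| Normal | 4.3% | 4.4% | shift of 0.2 SD | 70% | 68% |
| Lognormal | 4.3% | 4.9% | 25% larger scale | 55% | 77% |
| TLU-like | 6.1% | 5.8% | 25% larger scale | 41% | 18% |

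A second zero-inflated shape (50% zeros overall, lognormal with log-SD 1 among owners) shows the opposite ordering when only the ownership rate differs: at 45% v 55%, power is 23% for the t test and 61% for Mann-Whitney.

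Type I error is near nominal throughout. The Monte Carlo standard error at 5% is √(0.05 × 0.95 / 2,000) ≈ 0.5 percentage points. The power ordering changes with the assumed alternative.

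**The case against.** The strongest reply is that this is a drafting slip. The paragraph shows the intended direction when it says that nonnormal data "will be assessed for significance using the Mann-Whitney test", and few analysts would label a variable normal because a normality test rejected it. That is probably right about intent. It does not remove the error: the rule is explicit, nothing corrects it, and the other sentence only turns a wrong rule into a contradictory one.

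The reply is stronger on consequence, and three parts of it stand.

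- **TLU.** A reader might infer that the main exposure will be analysed by the wrong test. The documents do not support this. The rule is worded for outcome variables, and TLU is the exposure. It may be meant to cover TLU, because the outcome, stunting, is binary and defines the groups, but this is not stated. TLU is very likely skewed, being a weighted animal count in a study that admits children who "reside in a household with or without livestock", but no distribution is given. The power results do not show that the t test is the wrong choice for TLU either: the ordering reverses with the alternative assumed.
- **Main analysis.** The adjusted association is estimated by logistic regression, which the rule does not govern.
- **Summaries.** The plan already gives mean and SD for continuous baseline data and includes the mean for nonnormal data, so a mean would be reported under either direction of the rule.

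**Conclusion.** The decision rule is wrong as written and contradicts its own paragraph. That conclusion follows from the text and needs no assumption.

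Followed literally, the rule swaps the test for unadjusted continuous comparisons between stunted and nonstunted children, possibly including TLU. Under the assumed shapes the misrouting is close to complete at n = 614. The damage is bounded: type I error was 4.3–6.1% for the t test and 4.4–5.8% for Mann-Whitney at 307 per group, and the Fisher exact tests and the logistic regression are untouched. Power can move in either direction, so the figures support fixing the choice of test unambiguously in advance, not a claim that either test is right for TLU. The correction should be made, but it does not threaten the main adjusted result.

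**What to change.** Replace the decision sentence with text to this effect:

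> When the Kolmogorov-Smirnov test rejects normality (P ≤ .05), the variable is summarised by median and quartiles and the groups are compared with the Mann-Whitney test. When it does not reject, the variable is treated as normal and the groups are compared with the two-sided t test.

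Add one sentence saying whether the rule applies to TLU and other livestock counts, since the present wording refers only to outcome variables. Naming a test for TLU in advance without a pretest is a reasonable option, but it is a design preference and the correction does not require it.

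The cost is one or two sentences. No data item, sample size or participant is affected. The article plans data collection from November 2025, so the change is best made before any data are analysed.

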## Abstract

**Background:**

In resource-constrained environments where malnutrition in children is common, people coexist closely with livestock. Undernutrition, which can result in stunting, wasting, and being underweight, is still a major public health issue for children in India. Livestock serves as a direct source of protein through animal-source foods such as meat, milk, and eggs, which significantly reduce undernutrition in children younger than 5 years. The association between livestock ownership and stunting in children has not been explored well in Maharashtra, India.

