**Objective:**

This study evaluates the relationship between stunting among children younger than 5 years in central India and livestock ownership by using the Tropical Livestock Unit (TLU) score.

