Agriculture, with its allied sectors such as animal husbandry and livestock production, is India’s largest source of livelihood [10]. One integrated agricultural component that enhances household income, consumption, productivity, and food security is livestock [11]. Livestock provides protein directly through meat, milk, and eggs, known as animal-source food or indirectly by boosting the household income for food purchases [12]. Livestock ownership can improve the nutritional diversity and the quality of nutrition for households that own them, even though it may also raise the risk of environmental enteropathy, a condition linked to the loss of nutrients in the stomach, in children [13]. The Wardha district in Maharashtra is notable for its livestock and poultry farming, which is essential to the rural economy. According to the 20th livestock census, Wardha district recorded 489,836 animals, of which 344,875 are poultry and cattle units [14]. A few studies conducted in African nations have shown that owning more livestock can greatly boost the consumption of food items derived from animals and enhance nutritional outcomes [15,16]. Nonetheless, few studies [4,17] have been conducted in India to examine the relations between household livestock ownership and the stunting and nutritional status of children younger than 5 years. The tropical livestock unit (TLU), an index used in this study, is created by giving each animal a weight and merging all of the livestock characteristics for the household into a single variable [18]. Additionally, a dearth of studies [19] in Maharashtra examines the association between livestock ownership and stunting in children younger than 5 years. This study seeks to evaluate the relationship between stunting among children younger than 5 years in central rural India and livestock ownership by using the TLU index, considering existing research gaps.

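### Dietary habits and illness episodes are named as confounders although the protocol describes diet and enteropathy as routes by which livestock acts, so an odds ratio adjusted for them is not the overall association

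*Protocol article*

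**What the plan says.** The abstract's Objective reads: "This study evaluates the relationship between stunting among children younger than 5 years in central India and livestock ownership by using the Tropical Livestock Unit" score. The Introduction, Discussion and Conclusions repeat this aim. No direct or mediated effect is specified. The Conclusions say the result should guide policy, including whether to promote livestock ownership, and leave the pathways as hypotheses for later research.

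The abstract's Background gives the mechanism: "Livestock serves as a direct source of protein through animal-source foods such as meat, milk, and eggs, which significantly reduce undernutrition in children". The Introduction repeats it and adds income: "Livestock provides protein directly through meat, milk, and eggs, known as animal-source food or indirectly by boosting the household income for food purchases". It also names a possible harm of ownership: "it may also raise the risk of environmental enteropathy, a condition linked to the loss of nutrients in the stomach, in children".

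The Data Analysis section states that "All confounding variables will be analyzed using multivariable logistic regression" and that "confounding variables will be recognized and adjusted to understand the multiple factors that can influence the outcome (stunting"). Its examples are "confounding factors such as WASH; wealth index of the household; episodes of illness; dietary habits; knowledge, attitude, and practices regarding livestock; and livestock diseases". It closes by saying that "multivariable logistic regression will allow assessing the independent effect of each of the exposures".

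**The concern.** A confounder is a common cause of exposure and outcome, or stands in for one. A variable that the exposure changes, and that then changes the outcome, is a mediator. Adjusting for a mediator removes from the exposure coefficient whatever passes through it. The background presents diet, and in part child illness, as consequences of keeping animals. The analysis section treats the corresponding variables as nuisance factors to be adjusted away.

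What is at stake is the meaning of the adjusted TLU odds ratio. A decision about promoting ownership needs the overall association, including the part that comes through food. An odds ratio holding diet and illness fixed answers a different question. Even as a direct effect it is valid only if nothing unmeasured drives both the mediator and stunting. Reading every coefficient of one model as an independent effect compounds the problem: the diet coefficient and the TLU coefficient in that model do not have the same kind of interpretation.

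**Working it through.** The plan has no figure at stake here: its only calculation is the sample size, and this point does not depend on it. The check is a comparison of the text, followed by an illustration.

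**1. Each listed variable against the protocol's own account**

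- *Dietary habits.* Animal-source food is the stated route from livestock to nutrition (abstract Background, Introduction). Support as a mediator is strong.
- *Episodes of illness.* Enteropathy is a stated possible harm of ownership (Introduction), and the Discussion cites the spread of pathogens from livestock to humans. Support is good, though the protocol does not equate enteropathy with recorded illness episodes.
- *Livestock diseases, and livestock practices.* The Discussion cites a link between livestock disease and poorer growth but never calls it a pathway from ownership. The difficulty is structural: a household without animals has no livestock disease and no husbandry practice. If non-owners are coded as free of disease, the TLU coefficient partly contrasts non-owners with owners of healthy animals. If the item is left blank for them, the complete-data rule in the same section would drop them.
- *Wealth index and WASH.* These are plausible confounders. The income route makes wealth partly a mediator as well.

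**2. Illustration with assumed effects**

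The protocol gives no effect sizes, so every coefficient below is an assumption. With W wealth, X standardised TLU, D diet, I illness, and e independent standard normal errors:

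- X = 0.4W + √(1 − 0.16)·e
- D = a·X + 0.3W + e
- I = b·X − 0.2W + e
- logit P(stunted) = −1.0 + c·X − 0.4W + g·D + h·I

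The simulated population was 600,000, with about 30% stunted, sampled 1:1 as cases and controls. On the log-odds scale the wealth-adjusted total is roughly c + a·g + b·h, and the value after also adjusting for D and I is c. In row 3, for example, −0.1 + 0.4(−0.5) + 0.2(0.5) = −0.2, and exp(−0.2) = 0.82, against 0.83 simulated. The small gap arises because odds ratios are non-collapsible.

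| Scenario | a, b, g, h, c | OR per SD, adjusted for W | + D | + D and I |
|---|---|---|---|---|
| 1. All through diet | 0.4, 0, −0.5, 0.5, 0 | 0.83 | 1.00 | 1.00 |
| 2. Diet protective, illness half as strong and harmful | 0.4, 0.2, −0.5, 0.5, 0 | 0.91 | 1.10 | 1.00 |
| 3. As 2, with a direct effect | 0.4, 0.2, −0.5, 0.5, −0.1 | 0.83 | 1.00 | 0.91 |
| 4. Diet path and a stronger direct effect | 0.4, 0, −0.5, 0.5, −0.2 | 0.70 | 0.83 | 0.82 |
| 5. Weak paths, with a direct effect | 0.2, 0.1, −0.3, 0.3, −0.1 | 0.89 | 0.94 | 0.91 |
| 6. Equal and opposite paths | 0.4, 0.4, −0.5, 0.5, 0 | 1.00 | 1.21 | 1.00 |
| 7. No mediated path | 0, 0, −0.5, 0.5, −0.2 | 0.83 | 0.83 | 0.82 |

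**3. Reading**

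Where diet carries the effect, adjustment moves the odds ratio to 1 or towards it (rows 1 and 4). Where the paths are weak, absent or cancelling, adjusting for both changes little (rows 5 to 7). Direction is not fixed either. In rows 2 and 6, adjusting for diet alone leaves the harmful path open and gives an odds ratio above 1. Adjusting for illness alone in row 2 would leave about exp(0.4 × −0.5) = 0.82, further from 1 than 0.91.

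**The case against.** The strongest reply is that the section fixes no model. The list is given as examples, the factors are only to be considered, confounders are still to be identified, and no primary adjusted odds ratio is named. A fuller analysis plan might separate the models. This stands as a limit: it cannot be said that all six variables will enter one main model. It does not remove the point, because the text positively labels diet and illness as confounders and names no model without them.

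Second, dietary habits also reflect wealth, culture and maternal education, so they may carry some confounding. The Discussion also mentions missing dietary and livestock-health data as a possible reason for a small effect in an earlier study, which explains why these variables are measured. Both are fair. But wealth is already listed and sociodemographic data are collected, so that part can be addressed without closing the diet route, and measuring a variable does not require adjusting the main estimate for it.

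Third, unadjusted comparisons are planned too, so a reader who infers that a real benefit would be hidden goes too far. A crude association would appear beside the adjusted one. It would not be adjusted for wealth, however, so it does not supply the missing estimate.

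Three further inferences are not supported. Livestock disease is not shown to be a mediator. The absence of child age, sex and maternal factors from a list of examples is not an omission: the questionnaire covers the sociodemographic profile of child, mother and household, and the z scores already account for age and gender. A loss of power cannot be computed, because the protocol gives neither an effect size nor an ownership rate, and the problem is a change in the quantity estimated.

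**Conclusion.** The point holds in a limited form. The protocol describes diet, and as a possible harm enteropathy, as ways in which livestock affects child nutrition, and then names dietary habits and illness episodes as confounders. A TLU odds ratio conditional on them is at most a residual direct association and does not answer the stated objective. Livestock disease and owner-only practices cannot serve as ordinary confounders across owners and non-owners, for the separate reason that they are defined only among owners.

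The documents determine neither size nor direction. Under the assumed scenarios, adjusting for both variables moved the odds ratio by as much as 0.83 to 1.00 and by as little as 0.01 or nothing. The movement towards 1 is large if the benefit runs mainly through diet, which is the mechanism the protocol itself puts first. The conclusion rests on that described mechanism and on the analysis being carried out as worded. It should be corrected, but it does not threaten the design.

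**What to change.** - State one main model for TLU and stunting, adjusted for pre-exposure confounders from data already planned: for example household wealth index, WASH and sociodemographic factors. The wealth index should not count animals. Acknowledge that wealth may lie partly on the income pathway.
- Move dietary habits and illness episodes to a secondary model labelled as a direct-effect analysis, and state its assumption of no unmeasured mediator-outcome confounding.
- Analyse livestock disease, and practices that apply only to owners, among livestock-owning households.
- Drop the statement that one model gives the independent effect of each exposure. In the main model, interpret the TLU coefficient as the exposure association.

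The cost is revised wording, one additional model and slightly more analysis work. No new participants or measurements are needed, and the change can be made before data collection, planned from November 2025.

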**Methods:**

A community-based, case-control study will be conducted for 12 months among 614 children aged 6-59 months in a few rural blocks of Wardha district, Maharashtra. A predesigned semistructured questionnaire will collect data from the informant (either parent). Anthropometric measurements will be plotted on World Health Organization (WHO) standard growth charts for *z* scores for stunting and wasting. TLU will be used to represent the livestock count of all species. The categorical variables (stunted and nonstunted) will be analyzed using the Fisher exact test to find significant associations between different risk factors. All confounding variables will be analyzed using multivariable logistic regression. Associated risks will be identified and tabulated using the odds ratio with confidence intervals.

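### One mutually adjusted logistic model cannot give the independent effect of each exposure: factors whose consequences are also in the model, TLU included, get at most a residual direct-effect odds ratio

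*Protocol article*

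**What the plan says.** The Data Analysis section of the protocol article makes four linked statements.

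- Scope: "All confounding variables will be analyzed using multivariable logistic regression".
- Covariates: besides the livestock-stunting association, it names "or the impact of one or more confounding factors such as WASH", and the list goes on with "wealth index of the household; episodes of illness; dietary habits; knowledge, attitude, and practices regarding livestock; and livestock diseases will be considered". All of these carry the one label of confounder.
- Output: "Associated risks will be investigated and tabulated using the odds ratio with a confidence interval". The Methods paragraph of the abstract says nearly the same.
- Interpretation: "Essentially, multivariable logistic regression will allow assessing the independent effect of each of the exposures".

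No adjustment set is given for any single factor, and no separate model per factor is mentioned.

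**The concern.** A regression has one adjustment set, and a set that suits one coefficient need not suit another. If a factor works partly through a second variable and both are in the model, the first factor's coefficient shows only what remains once that route is held fixed. The coefficient of a factor at the end of the chain loses nothing in this way. The two rows then answer different questions, although the plan gives them the same name.

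This applies to the main exposure as well as to the covariates. Diet, child illness and livestock disease are listed as confounders of the livestock-stunting association, yet the protocol's own background describes routes of this kind from livestock to the child's growth. A TLU odds ratio adjusted for them does not estimate the overall association that the objective asks about.

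The statement is an affirmative claim about what the analysis delivers. It is therefore a point about the text as written, and not about detail that could be left to an analysis plan.

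**Working it through.** The point rests on no figure in the plan, and the sample size of 614 does not enter it. The check has two parts.

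**1. Causal order in the protocol's own background**

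| Step | Where it is stated |
|---|---|
| Repeated illness and poor long-term intake lead to stunting | Introduction |
| Livestock leads to animal-source food in the diet | Introduction |
| Livestock leads to household income, and income to food purchases | Introduction |
| Livestock may lead to enteropathy in the child | Introduction |
| WASH blocks the spread of pathogens to people | Discussion, Overview (conclusion of a cited poultry study) |
| Wealth leads to WASH; wealth leads to illness | Not stated; assumed here |

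So WASH has a consequence (illness) in the covariate list, wealth has at least one (diet), and livestock has several. Illness episodes need have none.

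**2. Illustration of direction and size**

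Inputs, all assumed except the stunting level of about 28%, which the Sample Size section uses:

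- One million children were simulated per scenario, then sampled 1:1 using all cases, so that sampling error is small. This shows bias, not power at 307 per group.
- W is wealth (standard normal). T is TLU, 0.3W plus standard normal noise. The rest are binary, with these log odds: WASH H, sW; diet D, sW + sT; livestock disease L, -1 + sT; illness I, -sH + sL - sD.
- Stunting has log odds -0.9 - 0.2W - 0.05T - 0.1H - sD + sI.
- The path strength s is 0.3, 0.6 or 0.9.

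One logistic model with all six variables was compared with a model per factor that adjusts only for what precedes it: wealth alone; TLU, WASH and diet each given wealth, with TLU added for diet; livestock disease given TLU and wealth; illness given all the others.

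| Factor | All six together (s = 0.3 / 0.6 / 0.9) | Preceding factors only (s = 0.3 / 0.6 / 0.9) |
|---|---|---|
| Wealth, per SD | 0.82 / 0.82 / 0.82 | 0.78 / 0.72 / 0.64 |
| WASH | 0.90 / 0.91 / 0.91 | 0.88 / 0.84 / 0.77 |
| Diet | 0.74 / 0.55 / 0.41 | 0.73 / 0.51 / 0.36 |
| Livestock disease | 1.00 / 1.00 / 1.01 | 1.03 / 1.08 / 1.19 |
| TLU, per unit | 0.95 / 0.95 / 0.95 | 0.93 / 0.88 / 0.83 |
| Illness | 1.36 / 1.82 / 2.46 | 1.36 / 1.82 / 2.46 |

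The loss on the log scale is 1 - ln(OR all six) / ln(OR preceding only). From the unrounded odds ratios:

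- Wealth: 1 - ln 0.819 / ln 0.779 = 20%; 1 - ln 0.821 / ln 0.716 = 41%; 1 - ln 0.819 / ln 0.635 = 56%.
- WASH: about 17%, 46% and 63%.
- TLU: about 28%, 59% and 70%.

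The mutually adjusted model recovers the direct coefficients that were put in: exp(-0.2) = 0.82 for wealth and exp(-0.05) = 0.95 for TLU. That is why the wealth row stays at 0.82 however strongly wealth acts through the other variables. The illness row does not move because its preceding-factors model is the six-variable model.

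**The case against.** **The plan does not strictly fix one all-in model.** The phrase "or the impact of one or more confounding factors such as WASH" leaves the covariate set open, and exact sets are often left to an analysis plan. This stands as a limit on the reading. It does not rescue the sentence, because the promise covers each exposure while all the factors are handled together as confounders.

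**Independent effect is customary shorthand for a mutually adjusted association.** A direct-effect reading is legitimate if it is labelled as one. The plan does not label it, and the same section speaks of impact and of factors that influence stunting.

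**Unadjusted comparisons are also planned.** The Fisher exact, t and Mann-Whitney tests would show wealth's crude association with stunting, so wealth would not vanish from view. This is fair for wealth. For WASH and TLU the crude comparison is open to confounding by wealth, so neither the crude nor the fully adjusted figure is the one wanted.

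**Stronger readings are tempting, but the protocol does not support them.**

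- A reader might infer that every odds ratio except TLU's is distorted. Illness at the end of the chain need not be, and the Introduction gives livestock its own routes through diet and income, so TLU is not exempt.
- A reader might infer that a ranking of determinants will be wrong and will mislead policymakers. No ranking is planned, and the policy sentence in the Conclusions concerns the livestock-stunting association.
- A reader might infer that wealth or WASH will come out non-significant. That depends on path strengths that the protocol does not give; with weak paths the shift is small (wealth 0.78 against 0.82).

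**Conclusion.** The concern holds for any factor whose consequences are in the same model: wealth, WASH, diet and livestock disease in the structure assumed here, and TLU itself. Their mutually adjusted odds ratios are at most residual direct effects and are not comparable with the row for illness. The plan's sentence therefore claims more than the model can give, and the tabulated odds ratios can be misread.

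The direction is usually toward 1, but not always. It needs the direct and indirect routes to run the same way, and for livestock the Introduction describes a helpful route through food and a harmful one through enteropathy. The size is not known. Over the assumed path strengths the wealth odds ratio moves from 0.78 to 0.82 at the weak end and from 0.64 to 0.82 at the strong end. The documents state the routes from livestock to diet and income, from income to food and from WASH to infection. The routes from wealth to WASH and to illness, and all path strengths, are assumptions.

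This merits a correction before analysis, since it decides what can be concluded from the main odds ratio and from the others in the table.

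**What to change.** Replace the closing sentence of the Data Analysis section with wording to this effect:

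*The primary logistic model estimates the odds ratio between TLU and stunting, adjusted for factors that precede livestock ownership. Diet, illness episodes and livestock disease are left out of this model and added only in a secondary model labelled as such. Coefficients of adjustment variables will not be interpreted as effects.*

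Two further steps complete it.

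- Justify including wealth in the primary model. It may precede livestock ownership, but the Introduction also has livestock raising household income. State in the same way whether WASH and livestock knowledge and practices are taken to come before or after ownership.
- If odds ratios for wealth, WASH or other factors are wanted, fit a separate secondary logistic model for each, adjusted only for factors that precede it (for example, WASH adjusted for wealth but not for illness).

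The cost is a change of wording and a few extra regressions on the same data, with no new measurements and no change in sample size. The downside is a results table with several models instead of one, and a causal order that has to be written down and defended.
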